## Discussion

### Principal Findings

This study evaluates the feasibility of a fully decentralized study model in a peripartum population, addressing practical barriers to participation in longitudinal microbiome research. Within this feasible framework, we anticipate exploratory, compositional alterations of the maternal gut microbiome following CS with PAP, most pronounced shortly after birth and attenuating over time. Given the limited and imbalanced sample size, these microbiome analyses are considered hypothesis-generating rather than confirmatory. In this context, the MAMA study exemplifies how to address practical barriers frequently encountered in peripartum research, including logistical challenges, limited time resources, and competing family responsibilities, which have made participation in longitudinal microbiome studies particularly difficult for pregnant women and new mothers.

We addressed these limitations by implementing a fully off-site study model that enables microbiome research during pregnancy and early motherhood—without requiring any in-person study visits. This approach not only facilitates participation across geographic and social boundaries but also integrates scientific inquiry into the realities of maternal life. The fully remote design, with telephone-based recruitment and postal sample return, was logistically feasible and well-accepted by participants. Particularly for pregnant women with limited mobility, young children, or those living far from clinical centers, the ability to participate from home appeared to have lowered the barrier to enrollment. Moreover, the participant-based approach allowed for maximum flexibility in scheduling the informed consent process. Participants were able to choose individually convenient times, including evenings and weekends, and rescheduling was possible at any time. In light of the exploratory nature and limited sample size, the primary contribution of this protocol lies in evaluating the feasibility of a fully remote study model in a peripartum population, while microbiome-related analyses are planned as secondary, exploratory outcomes.

Although digital data collection might be considered more efficient, a fully digital questionnaire system was not implemented due to institutional constraints and concerns regarding digital accessibility. Instead, paper-based questionnaires were included in each sample kit, aligning with the postal return of stool samples. This low-threshold approach ensured that participants could complete the forms directly when packaging their sample, without requiring technical equipment or online access. To maximize usability, all materials were written in plain language, following the principle of one idea per sentence, with no more than 15 words per sentence. Where possible, checkbox-style response options were used to reduce cognitive load and completion time.

Beyond logistical feasibility, participant acceptance also emerged as a relevant aspect of the remote study design, as several participants actively expressed interest in the study’s scientific goals and asked to be informed of the results. This feedback underscores the importance of building research models that are not only scientifically robust but also accessible, respectful of participants’ realities, and responsive to their curiosity and health concerns.

Despite growing awareness of the microbiome’s role in health, none of the participating women reported using probiotic supplements during the study period. This observation highlights a potential disconnect between perceived relevance and actionable guidance. The present study may provide a foundation for future research exploring the efficacy and safety of probiotic or dietary interventions during pregnancy and post partum.

At the same time, the implementation of a fully non–site-bound model presented specific challenges. In the VD group, it was difficult to anticipate the exact timing of delivery and thus ensure timely sample collection at T0 and T1. Participants were encouraged to prepare the sampling kit in advance and bring it to the hospital in their birth bag, but adherence to this instruction was not always possible. Additionally, logistical issues were encountered early in the study due to the use of time-limited digital postage codes. As these codes expired before participants mailed their samples, significant mailing delays occurred. The issue was resolved by switching to traditional postage stamps, which ensured reliable sample dispatch without further complications. Although this did not result in sample loss, it created confusion and required additional follow-up communication. These experiences highlight the need for practical guidance and reliable infrastructure when conducting off-site clinical research.

Recruitment was also affected by varying levels of institutional engagement across study sites. While the home-based design reduced participant burden, it still required initial support from clinical staff to initiate contact or distribute study materials. Staff at one study center demonstrated strong interdisciplinary cooperation, with committed medical professionals actively facilitating participant outreach. This differed significantly in the other study center, where limited personnel resources and skepticism about participants’ willingness to provide samples postpartum led to reluctance in supporting recruitment. This ultimately contributed to the premature closure of enrollment before the initially planned sample size was reached. This limitation in institutional support directly impacted the final sample size, which remained below target and unevenly distributed between the 2 study arms. In addition, several participants had to be excluded during the study due to protocol violations, such as postpartum antibiotic use identified retrospectively through questionnaire data, or delayed sample return beyond the predefined protocol windows. Despite these constraints, the sampling scheme captured three critical time points—before delivery, shortly after birth, and during postpartum recovery—enabling the identification of both acute and long-term changes in microbial composition.

While the observational design does not aim to establish causal effects, the resulting dataset is expected to yield meaningful insights into temporal microbiome dynamics in the peripartum period. Due to the exploratory nature of this observational study, no formal measures to control for bias resulting from group imbalance or participant dropouts were applied at the design stage. Potential confounding will be addressed during statistical analysis through stratification and adjustment, as appropriate. To this end, several relevant variables were prospectively recorded, including parity, medication or supplement use, diet, and allergies. Where numbers allow, these factors will be considered in stratified or adjusted analyses; however, residual confounding is likely given the modest and imbalanced sample size. Limitations in group comparability will be transparently addressed in the planned results publication in 2026.

### Limitations

Importantly, the modest and uneven sample sizes between study groups substantially limit statistical power and preclude confirmatory inference. As microbiome analyses are based on relative abundances derived from 16S rRNA sequencing, absolute bacterial load was not quantified; consequently, the lack of spike-in controls or quantitative PCR may affect the interpretation of apparent taxonomic enrichments or depletions. Consequently, microbiome-related analyses must be interpreted with caution, as they are susceptible to random variation and cannot reliably detect small or moderate effect sizes. This limitation directly informed the prioritization of feasibility outcomes as primary end points, while microbiome outcomes are framed as secondary and hypothesis-generating.

In addition, the unbalanced group sizes and incomplete longitudinal follow-up further restrict generalizability and limit the ability to perform robust subgroup or multivariable analyses. Consequently, the present study is not intended to provide definitive estimates of effect magnitude, but rather to delineate plausible patterns and inform the design of future, adequately powered investigations.

### Comparison With Prior Work

While several longitudinal studies have investigated peripartum changes in the maternal gut microbiome [9,32], existing evidence does not address the specific impact of CS and, in particular, PAP nor their potential association with dysbiosis in the postpartum period. This represents a relevant gap in current research [18], given the widespread use of antibiotic prophylaxis during CS. Microbiome dysbiosis is commonly characterized by compositional shifts, including reduced diversity and altered relative abundances of immunologically and metabolically relevant taxa. Such patterns have been associated with adverse pregnancy outcomes, for example, in preeclampsia, underscoring the potential relevance of maternal gut microbiome alterations during and after pregnancy [33].

Perturbations of the maternal gut microbiome induced by CS with PAP may have implications that extend beyond the immediate postpartum period. Pregnancy is characterized by profound metabolic and immunological adaptations that facilitate fetal tolerance while supporting increased maternal energy demands, processes that are closely intertwined with gut microbial composition [10]. While these adaptations are physiologically beneficial during pregnancy, alterations of the maternal microbiome in the postpartum period may be relevant for subsequent pregnancies. Evidence from a longitudinal cohort study suggests that specific gut microbiome patterns can precede the clinical diagnosis of gestational diabetes, indicating a potential link between microbial composition and later metabolic dysregulation [34]. In addition, dysbiosis in other maternal microbial niches, such as the vaginal microbiome, has been associated with pregnancy-related complications, including gestational diabetes, preterm birth, preeclampsia, and miscarriage [35]. Although these associations are exploratory and do not imply causality, they underscore the importance of longitudinal maternal microbiome research that extends beyond a single pregnancy.

Future studies may build on this protocol by recruiting larger and more balanced cohorts to enable adequately powered analyses. Incorporating absolute quantification approaches, such as quantitative PCR or spike-in standards, and extending longitudinal follow-up across multiple pregnancies would allow more robust assessment of maternal microbiome dynamics and their potential clinical relevance. The remote, participant-centered design evaluated here provides a feasible framework for such future larger-scale investigations.

### Conclusions

The MAMA study demonstrates the feasibility of conducting fully decentralized microbiome research in a peripartum population without requiring on-site study visits. By integrating recruitment, informed consent, and longitudinal sample collection into participants’ everyday lives through flexible, patient-oriented logistics, this protocol provides a practical and acceptable framework for maternal microbiome research during pregnancy and early post partum.

Given the exploratory design, modest sample size, and group imbalance, this study is not intended to support confirmatory conclusions regarding microbiome alterations following CS with perioperative antibiotic prophylaxis. Accordingly, microbiome-related outcomes should be interpreted as hypothesis-generating, while the primary contribution of this work lies in evaluating and documenting the feasibility of a remote study model in a clinically and logistically sensitive population.

By deliberately centering the maternal perspective and prioritizing maternal health, the MAMA study addresses an underrepresented aspect of perinatal research and illustrates that methodological rigor can be achieved alongside high accessibility for pregnant women and new mothers through an interdisciplinary approach. This framework enables future, larger-scale investigations aimed at robustly characterizing maternal microbiome dynamics and their potential relevance across and beyond pregnancy.

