**Conclusions:**

This protocol demonstrates the feasibility of conducting fully decentralized, longitudinal microbiome research in a peripartum population without requiring on-site visits. By integrating study procedures into maternal realities, the remote design reduces participation barriers and addresses a clinically relevant research gap that has remained largely unexamined despite routine use of PAP. While microbiome-related outcomes are exploratory, the methodological framework established here provides a scalable model for future maternal and postpartum research, supporting ethically grounded, participant-centered study designs and evidence-informed care strategies.

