### Ethical Considerations

The study was reviewed and approved by the ethics committee of Witten/Herdecke University (274/2021) in February 2022. A substantial amendment covering the addition of a second study center and modifications to the screening process was approved in September 2022. Recruitment commenced after ethical approval, with the first participant enrolled in May 2022, and the last participant in October 2023. Follow-up concluded in March 2024, with the return of the final stool sample. The remote consent procedure was explicitly reviewed and approved by the ethics committee. All participants provided verbal consent during the initial telephone screening and subsequently returned signed written consent forms together with their first stool sample. Study participation was voluntary, and participants could withdraw at any time without providing reasons. No incentives were provided for participation. All data were collected and processed in pseudonymized form in compliance with the General Data Protection Regulation (GDPR). No directly identifying information was accessible to the research team. The data protection concept was developed in collaboration with the institutional data protection officer and reviewed as part of the ethical application. There was no patient or public involvement in the study design or implementation. Pseudonymized raw data will be made available to qualified researchers upon reasonable request to the principal investigator and in accordance with institutional and GDPR requirements. The study was conducted as part of a doctoral project at the Faculty of Health, Witten/Herdecke University.

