### Statistical Analysis Plan

The following procedures specify how the predefined outcomes will be analyzed. The analysis will follow an exploratory framework. Although simple, biologically plausible hypotheses have been specified, no formal power calculation was performed. Consequently, results will be interpreted as hypothesis-generating rather than confirmatory.

Feasibility outcomes will be summarized descriptively using proportions, medians, and ranges. Timing of sample returns relative to the predefined collection windows (T0, T1, and T2) will be evaluated by calculating time intervals (in d) between the target and actual return dates. These intervals will be summarized using medians and IQR and compared between delivery groups where appropriate. Reasons for loss to follow-up (eg, no sample returned) will be documented, and analyses will be performed on available cases without imputation of missing data. This analysis will help assess protocol adherence and identify potential logistical barriers in the home-based study model.

To address the previously defined microbiome outcomes, the following statistical approaches will be applied: group comparisons between CS and VD will be performed for each time point (T0, T1, and T2) and longitudinally within participants as well as within groups, using all available paired samples (eg, T0-T1 or T1-T2), where applicable. Alpha diversity metrics (eg, Shannon index and Chao1 richness) will be compared using nonparametric tests (Wilcoxon rank-sum or Kruskal-Wallis test). Beta diversity will be evaluated using permutational multivariate ANOVA based on distance matrices (eg, Bray-Curtis and UniFrac). Visualization will include principal coordinates analysis.

Analyses will follow a 2-level structure, with primary community-level testing and secondary, exploratory taxonomic-level summaries.

Relative abundances of microbial taxa at different taxonomic levels will be summarized descriptively.

Exploratory differential-abundance analyses will be performed using ANCOM-II, a method suitable for sparse compositional data that incorporates its own procedures for controlling false discoveries. Taxonomic-level hypothesis testing will only be performed if community-level analyses indicate meaningful group differences.

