## Results

The recruitment and sample collection phase of the study has been completed. Between May 2022 and October 2023, a total of 37 participants were enrolled, including 25 women in the CS group and 12 in the VD group. Recruitment concluded below the originally planned sample size, reflecting real-world constraints in this peripartum population. Follow-up was completed with receipt of the final stool sample in March 2024. An overview of baseline characteristics of participants who returned at least one stool sample is presented in Table 1. DNA extraction and 16S rRNA gene sequencing were completed in a single batch in October 2024. All samples passed quality control and were retained for downstream analyses. An overview of included and excluded samples by group and time point is provided in Figure 2. Bioinformatic processing and statistical analyses were initiated in June 2025 and were ongoing as of December 2025.

**Table 1. T1:** Baseline characteristics of participants who submitted at least 1 sample (N=31)^a^.

Characteristic		Total (N=31)	CS^b^ with PAP^c^ (n=20)		VD^d^ without PAP (n=11)	
Continuous variables						
Age (y), median (IQR)		37 (33-39)	37 (33-39)		36 (33-38)	
Categorical variables, n (**%**)						
Delivery mode						
CS		20 (65)	20 (100)		—^e^	
VD		11 (35)	—		11 (100)	
Multiple births						
Yes		2 (6)	2 (10)		0 (0)	
No		29 (94)	18 (90)		11 (100)	
Parity						
0		12 (39)	9 (45)		3 (27)	
1		13 (42)	5 (25)		8 (73)	
2		5 (16)	5 (25)		0 (0)	
3		0 (0)	0 (0)		0 (0)	
4		0 (0)	0 (0)		0 (0)	
5		1 (3)	1 (5)		0 (0)	
>1		19 (61)	11 (55)		8 (73)	

a Only participants in the CS group received PAP; no antibiotics were administered in the VD group.

b CS: cesarean section.

c PAP: perioperative antibiotic prophylaxis.

d VD: vaginal delivery.

e Not applicable.

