**Figure 2. F2:**
[figure not shown]
Flowchart of participant enrollment, allocation, follow-up, and analysis in the MAMA (Microbiome Changes Due to Antibiotic Prophylaxis in Mothers at Birth) study, in line with the STROBE (Strengthening the Reporting of Observational Studies in Epidemiology) recommendations for observational studies. CS: cesarean section; VD: vaginal delivery.

A per-protocol sample was defined as a stool sample received within the prespecified time window and passing quality control. Protocol deviation was defined as exclusion from the per protocol set due to intake of antimicrobial agents (antibiotic or antifungal) other than the study medication or as sample collection outside the defined protocol windows and could not be assigned to a valid time point. Two women, who were initially allocated to the vaginal delivery group, delivered by CS and were therefore analyzed in the CS group; these women are counted under vaginal delivery at baseline (T0) and under CS at follow-up (T1 and T2). Numbers reported per group reflect participants analyzed at each time point; totals across groups were: T0 (n=31), T1 (n=19), T2 (n=21), and final analysis (N=71).

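### The article concludes that feasibility is demonstrated although it states no criterion and recruitment closed below target, and its enrolment denominator (37 or 31) is contradictory

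*Protocol article*

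**What the plan says.** The Objectives and Outcomes sections make feasibility primary. The indicators are the share of contacted women who enrolled, sample and questionnaire return at T0, T1 and T2, timeliness, and retention. The Statistical Analysis Plan section says "Feasibility outcomes will be summarized descriptively using proportions, medians, and ranges" and names no threshold.

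The Conclusions state that "The MAMA study demonstrates the feasibility of conducting fully decentralized microbiome research in a peripartum population without requiring on-site study visits". The Abstract has "This protocol demonstrates the feasibility of conducting fully decentralized, longitudinal microbiome research in a peripartum population". Eligibility and Recruitment, Results and the Discussion (Principal Findings) all report that enrolment ended short of the planned number.

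On who counts as enrolled, the sections differ:
- **Study Design and Setting** has the kit, with the consent form inside it, sent once a woman has been included.
- **Results** reports "a total of 37 participants were enrolled, including 25 women in the CS group and 12 in the VD group". Table 1 covers "Baseline characteristics of participants who submitted at least 1 sample (N=31").
- **Ethical Considerations** says that all participants gave verbal consent by telephone and "subsequently returned signed written consent forms together with their first stool sample". Eligibility and Recruitment describes the same route.
- **The Figure 2 legend** gives "totals across groups were: T0 (n=31), T1 (n=19), T2 (n=21), and final analysis (N=71") and says that these are participants analysed.

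On how feasibility became primary, Limitations says of the small, uneven sample: "This limitation directly informed the prioritization of feasibility outcomes as primary end points". The Rationale and the Study Design section say the same in substance. The Statistical Analysis Plan section refers to the outcomes as predefined.

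**The concern.** A claim that something is demonstrated needs a standard against which it was shown. The article states none. Its one visible benchmark for feasibility, the planned sample size, was missed. Elsewhere the article says more modestly that the study assesses or evaluates feasibility, so the headline goes further than its own framing.

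The second problem affects the primary estimates directly. If enrolment happens at telephone screening, 37 is the denominator and six women never returned a sample. If enrolment requires written consent mailed with the first stool sample, only 31 women can be enrolled. T0 return is then 100% by definition and says nothing about the remote workflow. Both statements cannot be true of the same set of participants.

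The article offers the design as a framework for larger studies. A team planning such a study would take its attrition allowance from these rates. The early postpartum sample at T1 matters most: two of the three stated hypotheses are T1 contrasts, and the third starts from T1.

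**Working it through.** **Inputs.** Enrolled: 37 = 25 CS + 12 VD (Results). Submitted at least one sample: 31 = 20 CS + 11 VD (Table 1). Analysed: T0 31, T1 19, T2 21, total 71 (Figure 2 legend).

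**The article's own totals reproduce.** 25 + 12 = 37; 20 + 11 = 31; 31 + 19 + 21 = 71.

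**The contradiction.** 37 − 31 = 6 enrolled women submitted no sample. If every participant returned written consent with a first sample, this number would have to be 0.

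**Rates under each denominator.** The rate is k/n. The exact (Clopper-Pearson) 95% limits are the 2.5% quantile of Beta(k, n − k + 1) and the 97.5% quantile of Beta(k + 1, n − k). When k = n the upper limit is 100%.

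| Analysed samples | Over 37 | 95% CI | Over 31 | 95% CI | Difference (points) |
|---|---|---|---|---|---|
| T0: 31 | 83.8% | 68.0 to 93.8 | 100% | 88.8 to 100 | 16 |
| T1: 19 | 51.4% | 34.4 to 68.1 | 61.3% | 42.2 to 78.2 | 10 |
| T2: 21 | 56.8% | 39.5 to 72.9 | 67.7% | 48.6 to 83.3 | 11 |

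Over all three time points the rate is 71/(3 × 37) = 71/111 = 64.0%, or 71/(3 × 31) = 71/93 = 76.3%, a difference of 12 points.

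**Retention.** The totals do not fix how many women have both later samples analysed. Among 31 women the number lies between 19 + 21 − 31 = 9 and 19. That is 24% to 51% of 37, or 29% to 61% of 31.

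**What the counts measure.** The legend's numbers come after exclusions. The Discussion mentions exclusions for postpartum antibiotic use and for samples outside the windows. The rates above are therefore analysable-sample rates. The text does not give the numbers returned at T1 and T2, so return rates cannot be calculated from it and may be higher.

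**The criterion.** No sample size, power or threshold calculation is stated, so there is nothing further to reproduce. With no cut-off, none of these rates can be classed as success or failure.

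**The case against.** There is a good deal to say on the other side, and much of it stands.

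- **A reader might infer that the figures show the design to be infeasible, or that T1 fell short.** The document does not support this. Without a criterion, 51% or 61% at T1 cannot fall short of anything. Only recruitment has a reference value, the planned size, and the article reports that shortfall openly, attributing it in part to limited institutional support at one centre.
- **A reader might take 19 and 21 as numbers returned.** They are numbers analysed. A kit sent back on time by a woman who later took antibiotics is a success for the remote workflow but drops out of these counts.
- **A reader might infer that no feasibility result is available, or that the stepwise counts are missing.** Several counts are reported in Results, and the analyses described as ongoing may be mainly the microbiome ones. Figure 2 is not shown here and may give returned and excluded samples by group. The original target may stand in a fuller protocol.
- **A reader might infer a concealed change of primary outcome.** The Rationale, Study Design and Limitations sections all disclose it. The word predefined in the Statistical Analysis Plan section can be read as pointing back to the Outcomes section.
- **The denominator conflict may be a slip in one sentence.** Inclusion by telephone, with 31 of 37 then returning a sample, is a coherent account, and the text nowhere reports a rate over 31.

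Two things remain. The claim of demonstration is affirmative, made twice about the primary outcome, and tied to no criterion. The consent sentence cannot be true of 37 participants, whatever Figure 2 contains.

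**Conclusion.** The point holds in this form: feasibility as a demonstrated conclusion is unsupported, though not refuted, and the denominator for the primary return rates is contradictory. The choice between 37 and 31 moves the analysable-sample rates by 10 to 16 points. At T1 the rate is 51% (34.4 to 68.1) over 37 or 61% (42.2 to 78.2) over 31, so the interval is wide under either choice.

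This rests on three assumptions. The legend totals count each woman once per time point. The 31 in Table 1 are the women who ever submitted a sample. No success criterion exists outside the article that the headline relies on without citing; if one does, the Conclusions should name it. I draw no conclusion by arm, because two women are counted under different groups at baseline and follow-up.

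**What to change.** 1. In the Abstract and Conclusions, replace *demonstrates* with *evaluates*. Report the observed rates together with the recruitment shortfall. Do not describe T1 as having fallen short.
2. Define enrolment once. The figure of 37 fits inclusion before the kit is sent, as Study Design and Setting describes; the sponsor should confirm it. Use that denominator for every feasibility rate.
3. Report returned and analysable samples separately at each time point, so that exclusions for antibiotic use are not read as failures of the postal workflow.
4. Reconcile Study Design and Setting, Ethical Considerations, Eligibility and Recruitment, Results and the Figure 2 legend. In particular, limit the statement on written consent to the women for whom it is true.
5. In the Statistical Analysis Plan section, add a sentence that the primary status of feasibility was set after recruitment, in line with what the Rationale, Study Design and Limitations sections already disclose.

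The cost is wording and one table, with no new data collection. The downside is a less favourable headline.
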